### 2.15. Establishment of a Data and Safety Monitoring Committee (DSMC)

A Data and Safety Monitoring Committee (DSMC) will be established. The committee will have the required expertise in paediatrics, neonatology, and trial design, but will not be involved in the care of study participants and would have no competing interests. The committee will monitor all the outcomes from recruitment until four months of age. The DSMC will review and approve the study protocol and will review all serious adverse events as they occur. No interim analyses are planned, but the DSMC will reserve the right to conduct an interim analysis or advise suspension or the termination of ongoing enrolment to this study.

### 2.16. Randomization, Allocation Concealment and Blinding

Group assignment will be allocated by a computer-generated, randomization sequence in randomly ordered block sizes of 2 and 4. Opaque, sealed, coded envelopes will be used for randomization. The neonates of multiple pregnancies will be considered as separate participants. Allocation concealment will be optimized by prescribing allocation only after informed parental consent and recording baseline neonatal data. The clinical trial pharmacist will supply the randomization sequence and sachets (identical design, weight, smell, and taste) containing either the triple-strain Bifidobacteria or placebo (equal volume of dextrin) manufactured by Morinaga Milk Industry Co., Ltd., Tokyo, Japan, to the healthcare personnel looking after the infants on the postnatal wards, and then to the parents. The parents will be educated about reconstituting the sachets and administering the probiotic or placebo at home and to monitor for any adverse effects. The hospital pharmacy will supply additional sachets to parents of participating infants as needed till the completion of the protocol (4 months of age). This will assure the masking of all investigators, clinical and non-clinical outcome assessors, midwifery and nursing staff, and the parents with regarding to the allocation of the enrolled infants.

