### 2.9. Sample Size Calculation

A sample size of 30 per group (total 60) was considered adequate to detect a 1.5-fold difference in alpha diversity with 80% power and a significance level of 0.05. By focusing on biological relevance, this sample size ensures that even subtle changes in microbial composition can be detected, providing a robust foundation for understanding the underlying biological mechanisms. This sample size allows for the detection of biologically meaningful variations in microbial composition, ensuring that differences in diversity metrics, such as Shannon diversity or Bray–Curtis dissimilarity, are statistically significant. By focusing on these well-defined biological parameters, this study can reliably capture important variations in microbial communities, providing a strong foundation for understanding their role in the system under investigation [21,22,23].

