### 3.7. Statistical Analysis of Clinical, SCFA, Bile Acid and Microbiome Data

Analysis will be based on the intention-to-treat principle. The continuous data will be summarized using median, interquartile range, and range. The categorical data will be summarized using frequency distributions. Univariate comparisons for the continuous data will be made using the Mann–Whitney test. For the categorical data, the Chi-square or Fisher exact test will be used.

The SCFA data will be analysed using a linear mixed model effect (LME) test to assess the differences between the groups over time. In this analysis, the subjects will be modelled as a random factor, and time and treatment are fixed factors. All the tests will be two-sided, and a *p*-value < 0.05 will be considered significant. The data on clinical outcomes will be analysed using SPSS version 22.0 statistical software (Armonk, NY, USA: IBM Corp.) and SCFA in R (version 3.5.1).

**Pre-planned subgroups:** (1) Infants who are born through caesarean section due to increased risk of gut dysbiosis. (2) Infants born to mothers with diet-controlled vs. insulin-dependent GDM. (3) Infants born to mothers with GDM and a normal vs. high BMI.

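### Co-twins are allocated separately, so most pairs would be split between probiotic and placebo in one home, and the named tests take no account of the shared mother

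*Protocol article*

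**What the plan says.** The rule for multiples is in section 2.16: "The neonates of multiple pregnancies will be considered as separate participants". The same section describes a "computer-generated, randomization sequence in randomly ordered block sizes of 2 and 4". No rule keeps siblings in one arm, and the eligibility and exclusion lists (sections 2.5 and 2.6) do not exclude multiples.

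Dosing takes place at home: "The parents will be educated about reconstituting the sachets and administering the probiotic or placebo at home". It is daily until four months of age (section 2.17). Probiotic and placebo sachets are made to be indistinguishable (section 2.16).

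The primary outcome (section 2.10) is the infant's own faecal microbiome at four months. The Introduction names the mother as the main source of the infant's microbiome.

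For the analysis, section 3.7 says: "Univariate comparisons for the continuous data will be made using the Mann–Whitney test". Categorical data get chi-square or Fisher tests. The one mixed model, for short-chain fatty acids, has the infant as its random factor. No term for mother or family appears, and section 2.9 makes no allowance for clustering.

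**The concern.** Two separate problems follow from the rule on multiples.

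- **Contamination.** In a split pair, a placebo infant lives for four months beside an infant receiving live bifidobacteria, with the same parents, milk and household. The protocol's own rationale, vertical and horizontal transmission, makes transfer between co-twins plausible. Two visually identical products in one home also make a mix-up hard to notice. Either would move the two arms closer together, and an intention-to-treat analysis cannot undo that.
- **Dependence.** Co-twins share mother, delivery and feeding, so their microbiome outcomes are expected to be correlated. The rank, chi-square and Fisher tests assume independent infants.

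At stake are an attenuated primary contrast and standard errors that do not match the design.

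**Working it through.** **Step 1. The plan's own figure.** Section 2.9 states: "A sample size of 30 per group (total 60) was considered adequate". The target there is a ratio of 1.5 in alpha diversity, at 80% power and alpha 0.05. It gives no standard deviation, so the figure can only be solved backwards.

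- Normal approximation: d = (1.960 + 0.842) × √(2/30) = 0.723.
- t-test: d = 0.736.
- With ln 1.5 = 0.405, the implied log-scale SD is 0.405/0.723 = 0.56 (0.55 by t-test).
- SDs of 0.4, 0.5, 0.6 and 0.7 would need 16, 24, 35 and 47 per group.

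The stated 30 per group is therefore neither confirmed nor refuted. Below, 80% power is taken as given and d = 0.736 is used as its equivalent.

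**Step 2. Probability that a pair is split.** Assume co-twins take consecutive envelopes. The chance of opposite arms depends on where the first twin falls in the block.

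- Block of 2: position 1 gives 1, position 2 gives 1/2; mean 0.750.
- Block of 4: positions 1 to 3 give 2/3 each, position 4 gives 1/2; mean (3 × 2/3 + 1/2)/4 = 0.625.
- Both block sizes equally likely: (1 + 1/2 + 2 + 1/2)/6 = 0.667. Simulation of 40,000 sequences gave 0.669.

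Simple randomisation would give 1/2, so small blocks split pairs more often.

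**Step 3. Dilution and power.** The article gives neither the number of pairs *m* nor the share *t* of the effect that reaches a split placebo twin, so both are assumed. The expected share of placebo infants with a treated co-twin is k = (2m/3)/30. The contrast shrinks to d × (1 − t·k). Power is from the noncentral t, 30 per group, two-sided 0.05.

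| Pairs (m) | k | t = 0 | t = 50% | t = 100% |
|---|---|---|---|---|
| 1 | 0.022 | 80% | 79% | 78% |
| 2 | 0.044 | 80% | 78% | 76% |
| 3 | 0.067 | 80% | 77% | 74% |
| 4 | 0.089 | 80% | 76% | 72% |
| 6 | 0.133 | 80% | 74% | 68% |

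Simulation of the Mann–Whitney test itself gave similar values: with full transfer, about 75% to 76% at 2 pairs, 71% at 4 and 66% to 67% at 6. The table covers only effect gained by the placebo twin. A mix-up could also take effect away from the treated twin, which is not modelled.

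**Step 4. Ignoring the pairing.** With C same-arm pairs, S split pairs and within-pair correlation ρ (assumed), the variance of the arm difference relative to independence is 1 + 2ρ(C − S)/60.

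For 4 pairs and ρ = 0.6:

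- All same-arm: 1 + 2 × 0.6 × 4/60 = 1.08; a nominal 0.05 test runs at about 0.059.
- All split: 1 − 0.08 = 0.92; about 0.041.
- On average, C − S = −4/3: 1 − 2 × 0.6 × (4/3)/60 = 0.973; about 0.047.

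Simulated Mann–Whitney type I error for 2 to 6 pairs and ρ from 0.3 to 0.8 (up to 0.6 at 6 pairs) was about 0.045 to 0.050, against 0.049 with no twins.

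**Step 5. Cost of allocating pairs together.** All pairs are then same-arm. With ρ = 0.6 the variance ratios at 3, 4 and 6 pairs are 1.06, 1.08 and 1.12. Power at d/√ratio is about 78%, 77% and 75%.

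**The case against.** The strongest reply is that individual randomisation of multiples is a stated, defensible choice that allows comparison within families, and that its cost is undocumented.

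- **Few pairs are likely.** Both twins must be born after 35 weeks, be predominantly breast-fed and pass the antibiotic exclusions. Zero to two pairs is compatible with the text.
- **Transfer and mix-up are not quantified.** Labelling sachets per infant is the kind of operational detail that a condensed article omits.
- **Sibling clustering could be handled in an analysis plan that is not shown.** The sentence on multiples is in the randomisation section and does not itself say how co-twins are analysed.
- **Co-allocation costs power too.** At ρ = 0.6 it costs about as much as 50% transfer does under the present rule: 77% against 76% at 4 pairs.

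Most of this stands, and it limits the size of the point. It does not remove it. The allocation rule is stated rather than missing, and the tests that are named do not use the within-family comparison that would justify splitting pairs.

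Three stronger readings are tempting but unsupported:

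- **That twins inflate false positives.** Most pairs are split, so the average error goes slightly the other way.
- **That power falls to 68%.** That is the corner of the range with 6 pairs and complete transfer, and it also assumes that transferred bifidobacteria carry the whole alpha-diversity effect.
- **That keeping twins together recovers power.** Step 5 does not show this.

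**Conclusion.** The point holds as a design weakness of limited and unknown size. Under the stated rule about two-thirds of twin pairs would be split within one household, given consecutive envelopes and equally likely block sizes. Any transfer or mix-up attenuates the primary contrast. For 1 to 6 assumed pairs the loss runs from none, through power of about 79% to 74% at 50% transfer, to 78% to 68% at full transfer. These figures rest on the stated 80% power, which cannot be checked without an SD.

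The independence error is small and slightly conservative on average. It becomes anti-conservative only if same-arm pairs happen to predominate. The case for change is therefore protection from attenuation and correctly sized standard errors.

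**What to change.** - **Section 2.16:** replace the sentence on multiples with: *The mother is the unit of randomisation; all infants of one pregnancy receive the same allocation.* Settle this before any twins are allocated.
- **Section 3.7:** account for the mother through a random mother effect or cluster-robust standard errors. For rank tests, use one value per mother.
- **Sensitivity analysis:** repeat the primary comparison with one infant per mother.

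If individual randomisation of twins is kept, the mother-level analysis and the sensitivity analysis still apply. For rank tests, the single value must then come from one chosen infant, because averaging a split pair would mix the arms.

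The cost is a short amendment, arms that may differ by one or two infants, and some loss of precision for same-arm pairs: a variance ratio of about 1.08 and power of about 77% for 4 pairs at an assumed ρ of 0.6.

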### 2.17. Probiotic Protocol

Enrolled neonates will be supplemented with the freshly reconstituted contents of the allocated sachets every day, which will be continued till four months of age. The dry, lyophilized powder in the sachets will be reconstituted using the mums’ own milk (first choice) or sterile water for injection. The dose will be 3 × 10^9^ CFU/day (1 mL reconstituted solution twice daily). Supplementation will be temporarily withheld if vomiting, diarrhea, or abdominal distension is noted.

The manufacturer, Morinaga Milk Industry Co., Ltd., are not a sponsor and will only supply the probiotic and placebo free for the trial and are not involved in the design, conduct, analysis, and reporting of the trial.

### 2.18. Ethics Statement

Approval was obtained from the Child and Adolescent Health Service Ethics Committee at Perth Children’s Hospital prior to commencing recruitment (RGS0000007074) in October 2024.

### 2.19. Trial Registration

This trial protocol has been registered (ACTRN12624000930583p) in the Australian Clinical Trials registry (ANZCTR).

### 2.20. Data Handling, Storage, Confidentiality

The National Health and Medical Research Council (NHMRC) Australian guidelines will be followed for confidentiality and data storage [32].

### 2.21. Reporting

The revised CONSORT guidelines will be used for reporting the results as highlighted in the EQUATOR (Enhancing the QUAlity and Transparency Of health Research) network [33].

## 3. Methods of Sample Collection, Processing and Analyses

The methodology for the Probiotics in Infants of Mothers with gestational Diabetes mellitus (PRIMD) trial will be identical to that reported in our previous RCTs [19,20].

### 3.1. Faecal Sample Collection

Stool samples will be collected from the diaper at two time points in sterile containers from each infant. The first sample (T1) will be collected as soon as possible after birth/admission to the postnatal ward (week 1). The second sample (T2) will be collected at the age of 4 months. All the samples will be labelled, weighed, and stored at −80 °C. After completing recruitment, the samples will be shipped on dry ice to the laboratory for storage at −80 °C and analyses. Acidified samples (5-fold in 1% phosphoric acid) will be shipped on dry ice to the laboratory for SCFA analysis.

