
## 2. Study Materials and Methods

### 2.1. Hypothesis and Aim

We aim to assess the effects of probiotic supplementation on the faecal microbiome composition of infants of mothers with GDM. We hypothesize that probiotic supplementation with triple-strain Bifidobacteria, 1 × 10^9^ CFU of each (*Bifidobacterium breve* M-16V, *Bifidobacterium longum* subsp. *infantis* M-63, *Bifidobacterium longum* subsp. *longum* BB536), will reduce dysbiosis compared to that of the control group. This will be assessed as an increase in the abundance of beneficial bacteria (e.g., bifidobacteria) and a reduction in the abundance of pathogenic bacteria (e.g., gammaproteobacteria).

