### 2.7. Intervention

Triple-strain Bifidobacteria: 1 × 10^9^ CFU of each (*Bifidobacterium breve* M-16V, *Bifidobacterium longum* subsp. *infantis* M-63, *Bifidobacterium longum* subsp. *longum* BB536) administered from birth till 4 months of age.

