### 2.10. Primary Outcome

Faecal microbiome composition will be estimated using 16S rRNA and shotgun sequencing. Baseline gut dysbiosis will be assessed at Timepoint 1 (T1: first week of life) by evaluating the ratio of beneficial to pathogenic bacteria, with reductions in dysbiosis measured at Timepoint 2 (T2: after four months of supplementation) in the probiotics group compared to the placebo group. The following variables will be analysed: (1) the presence or absence of specific species or pathways and clusters based on the unsupervised clustering of the gut microbial profile; (2) alpha diversity, richness, the abundance of particular species or pathways, and the differences in these numeric variables (treatment vs. baseline).

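### The T1 stool is the baseline of the primary outcome, but nothing requires it before the first sachet, so change-from-T1 results for bifidobacteria can be pulled toward no effect

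*Protocol article*

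**What the plan says.** The timing of T1 and the timing of the product are stated separately and never linked.

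- **T1 sample (Section 3.1):** "The first sample (T1) will be collected as soon as possible after birth/admission to the postnatal ward (week 1". The anchors are birth, ward admission and the first week. The first dose is not mentioned.
- **Product (Sections 2.7 and 2.17):** it is "administered from birth till 4 months of age", and "Enrolled neonates will be supplemented with the freshly reconstituted contents of the allocated sachets every day".
- **Role of T1 (Section 2.10):** "Baseline gut dysbiosis will be assessed at Timepoint 1 (T1: first week of life) by evaluating the ratio of beneficial to pathogenic bacteria". The variables listed for the primary outcome include alpha diversity, richness and abundances, and also "the differences in these numeric variables (treatment vs. baseline".
- **Order of events (Section 2.16):** concealment rests on "prescribing allocation only after informed parental consent and recording baseline neonatal data". This is the only ordering rule near allocation, and it does not name the stool sample.
- **Taxa (Section 2.1):** lower dysbiosis is to be seen partly as "an increase in the abundance of beneficial bacteria (e.g., bifidobacteria", which is the genus being given.

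Section 2.11 uses the same first-week timepoint for faecal short-chain fatty acids and bile acids.

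**The concern.** A baseline should be untouched by treatment. Here the sampling window and the dosing period overlap, so a stool taken some days into supplementation would comply with the text and still be called baseline. In the placebo arm this does no harm. In the probiotic arm the sample can contain the administered organisms, and these count directly as beneficial bacteria.

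Subtracting such a T1 removes part of the treatment effect in one arm only. For bifidobacteria abundance and for the beneficial-to-pathogenic ratio, the change-from-T1 contrast is then biased toward no effect. The first-week comparison of arms also stops being a clean check of balance, to the extent that samples are affected.

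The problem would surface late. Section 3.1 ships the samples for analysis only once recruitment is complete, when no pre-dose sample can be recovered. Unless the times of the first sachet and of the sample are recorded, the affected infants could not even be identified.

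**Working it through.** **Step 1: can a compliant T1 follow the first sachet?** Setting the sections side by side, supplementation starts at birth and is daily (2.7, 2.17). T1 is prompt but bounded only by week 1 (2.10, 3.1). Allocation waits for consent and neonatal data, not for stool (2.16). So the answer is yes. The text favours early sampling but does not secure a pre-dose sample.

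**Step 2: effect on each analysis.** Let Δ be the true between-arm difference at T2. Let f be the share of Δ already present in the probiotic arm's mean at T1:

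f = (share of probiotic infants sampled after dosing) × (share of the T2 effect present by then).

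The arms then differ by fΔ at T1, and the expected contrasts are:

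| Analysis | Expected contrast |
|---|---|
| T2 values alone | Δ |
| T2 adjusted for T1, with within-arm slope β of T2 on T1 | Δ − βfΔ = (1 − βf)Δ |
| Change from T1 | Δ − fΔ = (1 − f)Δ |

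The T2 comparison is unaffected. The adjusted analysis is affected in proportion to β, and the bias vanishes as β approaches 0. The change score takes the full loss. The article gives no value for β.

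**Step 3: the plan's own figure.** Section 2.9 states 30 per group for a 1.5-fold difference in alpha diversity, with 80% power and significance level 0.05; Section 3.7 makes tests two-sided. No SD or CV is given, so 30 cannot be reproduced. Solving backwards with the normal approximation:

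d = (1.960 + 0.842) × √(2/30) = 0.723 (0.736 with the noncentral t).

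On the log scale a 1.5-fold ratio then implies an SD of ln(1.5)/0.723 ≈ 0.56, a CV of about 0.61. This d serves only to fix a starting point of 80% power.

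**Step 4: power of a change-score analysis.** The change score is assumed to have 80% power at f = 0. Then

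power = Φ[(1 − f) × 2.802 − 1.960], and n per group to regain 80% = 30/(1 − f)², rounded up.

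| Sampled after dosing × effect present (both assumed) | f | Power | n per group for 80% |
|---|---|---|---|
| All T1 before dosing | 0 | 80% | 30 |
| 25% × 10% | 0.025 | 78% | 32 |
| 50% × 25% | 0.125 | 69% | 40 |
| 50% × 50%, or 100% × 25% | 0.25 | 56% | 54 |
| 100% × 50% | 0.50 | 29% | 120 |

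For example, at f = 0.25: 0.75 × 2.802 − 1.960 = 0.141, and Φ(0.141) = 0.556.

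**Step 5: what the article offers on f.** Section 2.2 reports that an earlier trial of this product, in term neonates with gastrointestinal surgical conditions, found a difference between arms after two weeks. Nothing is given for the first days of life, or for how many T1 samples would follow the first sachet. Both factors of f remain assumptions.

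**The case against.** The strongest case against is that the article leans toward early sampling. Section 3.1 asks for the sample promptly, with week 1 as a label for the timepoint, and the Abstract places the first fatty-acid sample at birth. Consent, baseline data, allocation and pharmacy supply must all come before the first sachet, so dosing cannot literally begin at birth. Section 3 says the methods follow two earlier trials, Figure 1 is not shown, and an article often leaves ward procedures to the full protocol.

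Much of this stands. A reader might infer that T1 may be taken freely at any point in the week. The instruction to sample promptly does not support that, and many T1 samples may in practice precede dosing. What does not fall away is that the article states its own T1 window in several places, always relative to age or admission, and that this window overlaps dosing. T1 itself needs consent, so the steps before the first sachet do not guarantee the order. A general reference to earlier trials does not override the window stated here.

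Two further inferences also go too far. One is that no baseline-adjusted analysis could escape the problem. As Step 2 shows, covariate adjustment carries only the contamination times the T1–T2 slope, which may be small. The other is that the whole primary comparison is compromised. Section 2.10 lists the numeric variables themselves as well as their differences from baseline, and Section 3.7 plans between-group tests, so a T2 comparison is available and unaffected.

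**Conclusion.** The point holds as a should-fix. The article calls T1 baseline, analyses change from it, and does not place it before the first sachet. For bifidobacteria abundance and the beneficial-to-pathogenic ratio, any resulting bias in change-from-T1 results is toward no effect, provided the early effect has the same direction as the effect at T2. T1-adjusted results are affected less, and T2 results not at all.

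The loss runs from negligible (78% power at f = 0.025) to large (29% at f = 0.50), and the documents do not say where in that range the trial would fall. A reader might take the larger losses as a forecast, or as losses for the alpha-diversity endpoint. Neither is supported. Both factors of f are assumed, and the effect size is back-solved from the alpha-diversity sample size, whereas the mechanism concerns bifidobacteria. The article gives neither the sign nor the size of an early effect on alpha diversity.

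**What to change.** 1. Define T1 in Sections 2.10 and 3.1 as a stool collected before the first study sachet. Reconcile Section 2.7 with that definition, and apply it to the fatty-acid and bile-acid baseline in Section 2.11. This concerns the sample only. It takes no position on when supplementation should start and asks for no change there.
2. Record the date and time of the T1 stool and of the first sachet for every infant.
3. Treat any T1 taken after the first sachet as a missing baseline, by the same timing rule in both arms and applied before unblinding. Keep the infant in the T2 comparison.
4. Report the number of such samples by arm.

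The cost is a ward instruction, two time fields on the case report form and one analysis rule. The downside is that some infants will have no valid baseline and drop out of change-from-T1 analyses.
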